# A type II implementation-effectiveness hybrid quasi-experimental pilot study of a clinical intervention to re-engage people living with HIV into care, ‘Lost & Found’: an implementation science protocol

**DOI:** 10.1186/s40814-020-0559-6

**Published:** 2020-02-21

**Keywords:** Implementation science, Implementation strategies, Out-of-care, Lost to follow-up, HIV, Nursing, Re-engagement

## Abstract

**Background:**

At the McGill University Health Centre (MUHC), 10% of patients living with HIV do not return for care annually. Currently, no formal system exists to re-engage out-of-care (OOC) patients. Lost & Found, developed using an implementation science approach, is an intervention to re-engage OOC patients. It is based on existing evidence-based interventions and will be adapted for use by nurses at the MUHC. The aims of this study are to simultaneously assess both implementation and effectiveness of Lost & Found in order to determine the viability of a future multisite stepped-wedge cluster randomised trial.

**Methods:**

Lost & Found consists of two core elements: identifying and contacting OOC patients. Based on formative work involving MUHC nurses, and the use of a combined implementation framework (enhanced Replicating Effective Programs, Tailored Implementation for Chronic Diseases, and Proctor et al.’s implementation outcomes), we will adapt the intervention to our clinic. Adaptations include the creation of an OOC risk prediction tool, an automated real-time OOC list, and prioritization of high-risk OOC patients for re-engagement. Delivery and ongoing adaptation of the intervention will follow a three-pronged implementation strategy consisting of (1) promoting adaptability; (2) planning, engaging, executing, evaluating, and reflecting cycles; and (3) internal facilitation. This 15-month quasi-experimental pilot study adopts a type II implementation-effectiveness hybrid design. To evaluate implementation, a convergent parallel mixed-methods approach will guide the mixing of qualitative and quantitative data at time points throughout the study. In addition, descriptive and pre-post analyses, for each of the implementation and sustainability phases, will inform evaluations of the cumulative effectiveness and sustainability of the Lost & Found intervention.

**Discussion:**

This study will provide preliminary evidence for (1) the utility of our chosen implementation strategies and (2) the effectiveness of the intervention. Ultimately, this information may be used to inform future re-engagement efforts using implementation science in other HIV care centres. In addition, the procedures and measurement tools developed for this study will be foundational to the development of a multi-site, randomised stepped wedge study that would provide more robust evidence in support of the Lost & Found intervention.

## Background

The UNAIDS 90-90-90 targets have set ambitious and necessary global goals for improving the HIV care cascade and tackling the HIV epidemic by 2030 [1]. The latter two targets seek to ensure that 90% of people diagnosed with HIV are prescribed combination antiretroviral therapy (cART) and that 90% of these people have suppressed HIV viral loads (VL). To accomplish these objectives, people living with HIV (PLHIV) must be engaged in care.

The cascade of HIV care has been assessed at the McGill University Health Centre (MUHC) in Montreal, Quebec. Since 2015, 10% of registered patients have not returned for care annually [2]. Furthermore, a formal system to re-engage these patients does not exist. Given the individual- and population-level health impacts associated with suboptimal HIV treatment adherence, as well as the socioeconomic repercussions, attrition from the HIV care continuum must be minimised [3–5]. Therefore, developing and testing interventions to re-engage PLHIV into care should be prioritised.

Criteria used for defining and identifying patients as out-of-care (OOC) vary greatly. For example, definitions based on absenteeism differ on the time period selected, from a few months to greater than a year [3, 6–9]. Also, these definitions do not account for relevant clinical factors such as CD4 cell counts, viral load test results, and comorbidities, all of which may influence risks for negative HIV-related outcomes.

A definition for OOC that combines time- and patient-related characteristics could better inform patient-level HIV care trajectories. Using electronic medical record data on medication adherence, last care appointment, substance use, recent CD4 count, prior cART exposure, and treatment failure, Robbins et al*.* created a Risk Prediction Tool (RPT) to predict and stratify patients by risk of HIV viremia [10]. This RPT was later used to effectively predict patients’ risk of missing HIV care appointments [11].

Few interventions have been tested to re-engage PLHIV who are OOC. Upon identification and documentation of OOC patients—a necessary first step in re-engagement efforts—phone calls appear to be a simple and effective method for contacting and re-engaging OOC patients [3, 8, 9, 12]. Previous studies have used phone calls as part of a package of methods for contacting patients without evaluating their effectiveness alone [3, 8, 9, 12]. One of these studies attempted multiple phone calls (no more than three) over an undefined period of time [12]. Therefore, there appears to be evidence for using (1) clinical and administrative data to identify OOC patients and (2) phone calls to re-engage these patients into care.

In previous attempts to identify and re-engage OOC patients, MUHC nurses faced several barriers to implementation and sustainability, including competing priorities and limited resources (e.g. staffing shortages, technological limitations, and insufficient decision support). Among these re-engagement efforts was a manual, patient-by-patient assessment of the need for re-engagement using a paper list of all CVIS patients. Due to the abovementioned barriers, the nurses found it difficult to maintain this list and assure follow-up. Re-engaging OOC patients is considered within the scope of nursing practice and, despite a lack of formal or systematic efforts by nurses in the current model of care, their involvement in re-engagement efforts is likely to be key. Indeed, their clinical experience and knowledge about patients could be helpful in determining how and when patients should be re-engaged into care [13, 14].

## Lost & Found: an evidence- and stakeholder-informed intervention

Lost & Found is an intervention to re-engage OOC patients into HIV care. It was developed using an implementation science approach and will be implemented between 2018 and 2019 to improve the current standard of care. This intervention makes use of evidence-based interventions and adapts them for staff and the perceived needs of patients at the MUHC.

Adaptation of this intervention is promoted by differentiating its core elements from its adaptable peripheral components, consistent with processes of established implementation frameworks [15, 16]. Core elements are “the critical features of the design and intent of the intervention that are thought to be responsible for the intervention’s effectiveness” [15]. Peripheral components are aspects that can be flexibly adapted for different settings and that respond to observed challenges during delivery [15].

There are two core elements of the Lost & Found intervention: I. Identifying and documenting OOC patients and II. Contacting OOC patients. Within each core element, there are peripheral components which can be adapted during delivery. These are listed in Table 1.

**Table 1 Tab1:** Peripheral components of each core element

I: Identifying and documenting OOC patients	II: Contacting OOC patients
1. OOC risk prediction tool 2. Automated, real-time list of OOC patients 3. Integration into the clinical EMR	1. Prioritization of higher risk patients 2. Nurse-led re-engagement 3. Nurse-delivered phone calls to OOC patients 4. Multiple contact attempts 5. Motivational communication

*OOC* = out-of-care; *EMR* = electronic medical record

### Core element I: Identifying and documenting OOC patients

We developed a two-step OOC risk prediction tool (OOC-RPT) to identify OOC patients for care re-engagement (Fig. 1). The tool is based on evidence from the United States Department of Health and Human Services (DHHS) HIV treatment guidelines and was developed collaboratively with our primary Lost & Found stakeholders, MUHC nurses [17].

**Fig. 1 Fig1:**
[figure not shown]
OOC risk prediction tool (OOC-RPT)

In step one of our OOC-RPT—“Triage”—all MUHC PLHIV are automatically classified daily as either high risk (red), intermediate risk (yellow), or low risk (green). These risk categories are informed by patients’ clinical characteristics. The OOC-RPT categories determine priority for re-engagement and are informed by the risk of disease progression. Patients are then classified as potentially OOC, based on time since their last appointment. Additional file 1 details the evidence supporting the use of these three categories and related criteria.

In step two—“Nurse Validation”—patients identified as potentially OOC are reviewed and confirmed as such by nurses. The need and urgency for re-engagement is determined based on risk category, information contained within the patient’s chart, and clinical judgement. Nurses’ knowledge of patients’ sociodemographic, psychosocial, and clinical factors, travel plans, shared care or other care arrangements, homelessness, mental illness, and/or chronic illness will help inform the confirmation of OOC status. All information related to follow-up of OOC patients will be documented in the clinic’s electronic medical record database, called RISQ (Réseau d’Informations Scientifiques du Québec).

The OOC-RPT will be programmed into RISQ to automate identification of OOC patients and provide a real-time list of OOC patients. Patients will be listed from high to low risk, helping nurses prioritize re-engagement efforts.

### Core element II: Contacting OOC patients

Clinic nurses will telephone patients using available contact information (RISQ, other hospital databases). They will receive a half-day of training from an expert in motivational communication, an essential skill for motivational interviewing. This training will help nurses encourage re-engagement through effective questioning, empathy, non-judgemental curiosity, guiding language, and adapted messaging [18]. This training is intended to provide nurses with additional skills or to strengthen existing skills for phone calls. It will be used at their discretion.

Patients who are reached by telephone will be scheduled for an appointment within timeframes dependent on their OOC-RPT risk category. However, earlier follow-up may be necessary as determined by clinical judgement. Patients in the high-risk category will be scheduled to be seen by a clinic nurse within 24-48 hours for basic primary care and phlebotomy (laboratory testing), and with their regular physician provider within one week of the nursing visit, for a full clinical assessment. Should the clinical situation suggest a need for more urgent care, the patient will be assessed by the walk-in physician on the same day as the nursing visit. Patients in the intermediate-risk category will be scheduled for an appointment within approximately two to four weeks of the telephone call, while patients in the low-risk category will be seen within four to six weeks. Patients who miss a scheduled appointment will be contacted the same day and provided another appointment, within timeframes depending on their risk category.

Attempts to contact patients will be made every 1, 2, and 4 weeks, for the high-, intermediate-, and low-risk categories, respectively. This pattern will be repeated until patients are contacted. Attempts to re-engage unreachable OOC patients will continue for up to 6 months (based on the maximum time a person can be outside of Quebec and still retain health care coverage), after which no further contact attempts will be made [19]. Nonetheless, these patients will remain on the OOC list until they return to care or until there is sufficient information to determine their care status. In all cases, nurses can modify the contact frequency and/or period based on individual patient factors.

## Proposed implementation of Lost & Found

We will use an implementation science approach to facilitate the adaptation and evaluation of Lost & Found in our clinic [16]. The findings from this study will highlight implementation strategies leading to successful local adaptation and real-world effectiveness [20].

### Implementation frameworks

Prior to selecting our implementation strategies, we developed a combined implementation framework for designing, implementing, and evaluating our clinical intervention and related implementation. It integrates elements of the following frameworks: enhanced Replicating Effective Programs (eREP) [21], Tailored Implementation for Chronic Diseases (TICD) [22], and Proctor et al.’s implementation outcomes [23]. eREP was used as the “process” framework to guide implementation of the intervention, TICD was utilised as the “determinants” framework to assist in understanding or explaining what might influence implementation, and Proctor et al.’s taxonomy of implementation outcomes was used as the “evaluation” framework [24]. Details regarding this combined implementation framework are outlined in Additional file 2. Based on formative work with MUHC nurses and the use of TICD worksheets [22], we identified 22 determinants (i.e. barriers and facilitators) that could impact the overall implementation of Lost & Found. We then categorised each determinant into the eREP phases (pre-implementation, implementation, or sustainability) based on when determinants were likely to have the greatest impact. Thereafter, this information was used to guide the selection of implementation strategies and related outcomes.

### Implementation strategies

We chose three core implementation strategies from available frameworks and inventories (eREP [21], TICD [22], and the Expert Recommendations for Implementing Change (ERIC) [25] project). These include (1) promoting adaptability; (2) planning, engaging, executing, evaluating, and reflecting (PEEER) cycles; and (3) internal facilitation. The times when these strategies will be used, relative to the eREP phases, are depicted in Fig. 2. Additional file 2 provides detailed descriptions of each implementation strategy and considers Proctor et al.’s guidelines for specifying and reporting implementation strategies [26].

**Fig. 2 Fig2:**

Implementation strategies by eREP implementation phase

#### Promote adaptability

During the pre-implementation phase, we customised and packaged the intervention into core elements and adaptable peripheral components (Table 1) [25]. The intervention, consisting of two core elements (i. identifying and documenting OOC patients, and ii. contacting OOC patients) and corresponding peripheral components, will be adapted to our setting over time. For example, the OOC-RPT (Fig. 1) and the role of nurses in re-engagement may change throughout implementation. This strategy helped prepare the intervention for adaptation and is an essential step in the eREP framework (Fig. 2) [21].

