#### Planning, engaging, executing, evaluating, and reflecting cycles

We will make frequent changes to the peripheral components of the intervention through co-occurring cycles of planning, engaging, executing, evaluating, and reflecting (PEEER) initiated by nurses, the internal facilitator, or other research and clinical staff [16]. PEEER is the process through which adaptations to peripheral components of the intervention occur. This implementation strategy is often referred to as cyclical small tests of change [25]. PEEER may continue informally after implementation, leading to ongoing adaptations if needed.

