#### Participants

All MUHC patients in the RISQ database during the 12-month implementation phase and the first three months of the sustainability phase will be included in analysis i). For analysis ii), we will retrospectively apply the OOC-RPT, excluding the nurse validation step, to patients in the year prior to implementation in order to create a pre-implementation comparison group. Thus, we will include all patients categorised as OOC by the OOC-RPT from one year prior (2017-2018) and to the end of the implementation phase (late 2019) in this analysis. Patients labelled as OOC before or after this time frame will receive the Lost & Found intervention, but will be excluded from the analysis because they did not become OOC within the time frame of the analysis. Based on the number of patients who were identified as not having had care appointments in 2016, we estimate approximately 25–30 patients will be identified as potentially OOC each month during the implementation of Lost & Found. In analysis iii), MUHC patients categorised as OOC from three months before the end of the implementation phase to the end of the sustainability phase (three months) will be included.

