#### Data analysis

i)Descriptive analysis

To assess cumulative effectiveness during implementation and sustainability, descriptive statistics (e.g. counts, proportions, medians, and inter-quartile ranges) will be reported.
ii)Pre-post analysis: Implementation phase

For this analysis, the second step of the OOC-RPT – nurse validation - will be ignored to ensure comparability between the two groups. This is done because nurse validation was not possible prior to the implementation of changes to the RISQ software. While this will result in a non-differential bias (to the null), it will simultaneously prevent a possible differential bias introduced from the nurse validation step of the OOC-RPT. To account for the impact that contact attempts could have on future follow-up behaviours, we will consider only the first OOC event for each patient. We will compare the re-engagement rates of OOC patients identified from our retrospective application of the OOC-RPT in the pre-implementation phase to re-engagement rates of OOC patients identified by step 1 of the OOC-RPT in the implementation phase. If the intervention is effective, we will find a statistically significant difference in the probability of re-engagement for OOC patients during the 12-month implementation phase compared to the year prior.

The impact of the complete Lost & Found intervention (i.e. both core elements) and implementation strategy on the proportion of OOC patients re-engaged will be examined in a Poisson model with robust variance estimation, using the year prior to implementation for comparison (see Eq. 1):
1$$ \log \left(\mathrm{R}\right)={\upbeta}_1\ast \mathrm{Imp}+{\upbeta}_2\ast \mathrm{Sex}+{\upbeta}_3\ast \mathrm{Age}+{\upbeta}_4\ast \mathrm{Canada}+\upmu +\log \left(\mathrm{C}\right) $$

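### Analysis ii does not fix which version of the out-of-care tool's step 1 defines the two cohorts, although the tool may change during the implementation year

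*Protocol article*

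**What the plan says.** **The tool can change.** Table 1 puts it first among the adaptable components of core element I: "1. OOC risk prediction tool 2. Automated, real-time list of OOC patients". The section Promote adaptability gives it as an example: "the OOC-RPT (Fig. 1) and the role of nurses in re-engagement may change throughout implementation". The section on planning, engaging, executing, evaluating and reflecting cycles adds: "We will make frequent changes to the peripheral components of the intervention".

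**The tool also defines the analysis set.** For the comparison year, Aim 2, Participants states: "we will retrospectively apply the OOC-RPT, excluding the nurse validation step, to patients in the year prior to implementation". Aim 2, Data analysis, ii) compares that group with "re-engagement rates of OOC patients identified by step 1 of the OOC-RPT in the implementation phase". The number of out-of-care patients enters Equation 1 as the offset C.

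**Stated measures for comparability.** Analysis ii ignores nurse validation (step 2) and uses only each patient's first out-of-care event. The plan assumes that the intervention leaves the rate of out-of-care classification unchanged, and will check this before the analysis. Changes to adaptable components go into the internal facilitator's logbook. For analysis iii only, few such changes are expected in the last three implementation months.

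None of these sections names a version of step 1 for either year.

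**The concern.** One algorithm serves both as part of the intervention, free to adapt, and as the case definition for the effectiveness estimate. Adapting the tool is legitimate in this hybrid design. The weakness is that the analysis definition is not kept separate from the clinical tool.

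If a step 1 criterion changes during the year, patients with a different underlying chance of returning enter or leave the implementation cohort, while the retrospectively built cohort may not change in the same way. β1 then mixes the change in definition with any effect of the intervention.

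This matters because re-engagement is the primary outcome of analysis ii, a significant result would count towards the viability of a larger trial, and the results are meant to inform its power calculation.

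**Working it through.** **1. Is a version fixed?** The plan states no effect size, power or return rate, so there is no figure to reproduce. The check is to set the sections side by side.

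- The pre-year cohort is a retrospective run of the tool, version not named.
- The implementation cohort is those picked up by step 1 during that phase, version not named. Core element I describes daily automatic classification and a real-time list, so live flags are the natural reading, though not a stated rule.
- Changes to the tool are allowed in exactly that phase.

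**2. Do the stated measures cover it?**

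- Dropping nurse validation makes step 2 comparable and leaves step 1 open.
- Using the first event only, under live flagging, ties each patient to the version in force when first flagged.
- The rate check sees how many are flagged, not who they are.
- The bias-to-the-null argument (Data analysis ii and Limitations) needs similar misclassification in both years. A change of definition in one year is differential.
- The logbook could date a change, but no analysis rule uses it.

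**3. Size of bias with no true effect.** Let p_A be the return rate under the version used for the pre-year, p_B the rate among patients brought in by a revision, and w their share of the implementation cohort:

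RR = [(1 − w)·p_A + w·p_B] / p_A

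All rates are assumptions.

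*Change halfway, equal numbers flagged before and after (w = 0.5), p_A = 0.60, p_B = 0.45:* (0.30 + 0.225)/0.60 = 0.525/0.60 = **0.875**. With w = 0.25 it is 0.5625/0.60 = 0.94; with w = 0.75 it is 0.4875/0.60 = 0.81. The reverse change (p_A = 0.45, p_B = 0.60, w = 0.5) gives 0.525/0.45 = 1.17.

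**4. Can the rate check miss it?** Aim 2, Participants expects 25–30 potentially out-of-care patients a month, so 25 × 12 = 300 to 30 × 12 = 360 a year. Assume the same number in the pre-year, p_A = 0.40, and a revision that swaps a share w for patients returning at 0.70 while the count stays the same. For w = 0.20 the rate becomes 0.80 × 0.40 + 0.20 × 0.70 = 0.46, and RR = 0.46/0.40 = 1.15.

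The false-positive probability comes from an unadjusted two-proportion test at two-sided 5% (also assumed). With n = 300:

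- pooled rate (0.40 + 0.46)/2 = 0.43; null SE = √(0.43 × 0.57 × 2/300) = 0.0404
- SE under the two rates = √[(0.40 × 0.60 + 0.46 × 0.54)/300] = 0.0403
- Φ[(0.06 − 1.96 × 0.0404)/0.0403] = Φ(−0.48) ≈ 0.32; the other tail is negligible

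| Share swapped | Spurious RR | False positive, n = 300 to 360 per year |
|---|---|---|
| 10% | 1.075 | 12–13% |
| 20% | 1.15 | 32–37% |
| 30% | 1.225 | 60–68% |

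The count is unchanged in every row, so the rate check sees nothing.

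If instead the revision adds 10% more patients who return at 0.70, RR = (0.40 + 0.07)/1.10/0.40 = 1.07. The count difference gives z = 30/√630 = 1.2 (n = 300) or 36/√756 = 1.3 (n = 360), which would probably not be noticed. Adding 20% more patients who return at 0.20 gives (0.40 + 0.04)/1.20/0.40 = 0.92, the opposite direction.

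**The case against.** The other side has several fair points.

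- *The article never says that two versions will be used.* A reader might infer that implementation patients will be flagged by a succession of live versions and pre-year patients by one other version. The text does not state this, and a single version run over both years would also fit the Participants section. That stands: the text shows that the definitions can differ, not that they will.
- *Step 1 may not be what changes.* The tool has two steps, and a change to step 2 would not touch analysis ii. That also stands, but nothing exempts step 1.
- *Late data entry.* A reader might add that visits recorded late would create live flags that soon appear to resolve. Nothing in the article mentions entry delay, so this forms no part of the point.
- *Analysis iii.* A reader might extend the point there unchanged. Analysis iii keeps nurse validation in both arms, so step 1 alone is not its case definition, and few changes are expected in its reference period.
- *Larger bias.* A revision in force for the whole year would give 0.45/0.60 = 0.75 with the first set of rates. Nothing suggests that the pre-year would be run with a version never used in the implementation year.
- *Safeguards.* The logbook would let a change be identified, and the rate check could show one that shifts the count. Both help, but neither fixes the definition.
- *Detail for another document.* The additional files, the full protocol and any SAP are not shown and might hold a version rule. But the article itself sets out how the two groups are made comparable, secures step 2 for that purpose, and declares the whole tool open to change.
- *A pilot.* A non-significant result does not rule the intervention out, and viability also rests on implementation scores. This lowers the stakes, but a significant result still counts in favour.

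**Conclusion.** The point holds for analysis ii. Step 1 of the tool defines the denominator in both years, the protocol allows the tool to change during one of them, and no version is fixed for the analysis. If step 1 criteria change, the risk ratio can be biased in either direction, and the planned measures do not reliably reveal it.

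The size cannot be derived from the documents. Under the assumed rates, spurious risk ratios run from about 0.81 to 1.23. They depend on the share of patients affected and on how different their return rates are. The false-positive figures also assume 300–360 patients in each year, an unadjusted test and a two-sided 5% level. If step 1 never changes, or if one version is in fact run over both years, this source of bias is absent.

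**What to change.** **Analysis ii**

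1. Name one dated version of step 1 as the analysis definition, for example the launch version.
2. Apply it retrospectively, from the same RISQ extract, to both the pre-year and the implementation year, whatever version the live tool was using.
3. Run the check on the rate of out-of-care classification on that fixed definition.
4. Report logged changes to the live tool, with a sensitivity analysis based on live flags.

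With one version in both years, a change to the live tool contributes no bias through the definition. The tool can go on adapting for clinical use.

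**Analysis iii**

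Validation status exists only for patients whom nurses reviewed, so re-running a fixed version would flag some patients without it. Here, report from the logbook whether step 1 changed during the six months compared. If it did, add a sensitivity analysis restricted to validated patients who also meet the fixed step 1 version.

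**Cost**

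A short addition to the plan and one further run of an algorithm that is already to be run retrospectively on the pre-year. The downside is that some analysed patients will never have appeared on the live list and so could not have been contacted through it, which dilutes the estimated effect somewhat. The live-flag sensitivity analysis helps to show by how much.
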